### Data management and analysis

For the feasibility analysis, the results will be expressed as percentage and numbers referring to adherence, recruitment rates, and safety, respectively. After qualitative data collection, two authors will perform the total transcription of the audios and notes line-by-line. Then, two authors will start the codification of the *corpus.* After transcription, the corpus will be codified in numbers and their respective groups (e.g., # ID1emp, # ID5cph) by a blinded third researcher, for the later analysis by a fourth researcher. Codes will then be consolidated into categories after an extensive exploration of the material and interpretation of the data obtained according to thematic analysis of the content. From this, entire research team will discuss to formulate inferences.

To verify the preliminary effectiveness regarding quantitative outcomes, the descriptive analysis will be performed with frequency, central tendency, and variability (mean and standard deviation or median and interquartile interval) in the statistical program SPSS 20.0 for Windows (IBM-USA). All results of the preliminary efficacy of the feasibility trial will be described as estimates of 95% confidence interval. An intention-to-treat analysis will be done with participants including who eventually will be missed in any part of the study.

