Based on all information above, this study presents the EMPOWER-PD protocol, a physical therapy approach based on the individual preferences. As a new intervention protocol, it is necessary to verify it feasibility when applied to the target population. This study presents the design of the feasibility randomized controlled trial that aims to(i)Investigate the feasibility of the EMPOWER-PD protocol through adherence rate, recruitment rate, and safety.(ii)Compare the preliminary effectiveness of the EMPOWER-PD with the conventional physical therapy through qualitative analysis of motivation, empowerment of health, followed by the analysis of the dependency of professional supervision by individuals to remain active in the post follow-up period.(iii)Compare the preliminary effectiveness of the EMPOWER-PD in motor and non-motor symptoms (functional mobility, gait, fatigue, aerobic capacity/endurance) with the conventional physical therapy through quantitative analysis of estimates of 95% confident interval.

We hypothesize that the EMPOWER-PD will lead to higher adherence and safety when compared with conventional physical therapy. Concerning motivation, health empowerment and dependency of professional supervision by individuals to remain active in the post follow-up period, we hypothesize that the EMPOWER-PD will be associated with better outcomes in preliminary effectiveness than the conventional physical therapy. For the motor and non-motor symptoms, we hypothesize that the EMPOWER-PD will be associated with similar preliminary effectiveness to the conventional physical therapy.

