#### Randomization

A computerized block randomization procedure will be implemented by a blind researcher. Individuals with PD will be randomly allocated to two arms: (a) EMPOWER-PD or (b) conventional physical therapy (CPh). An independent person will notify the treating physiotherapists by email to ensure concealed allocation. The distribution of the groups will be kept in a closed envelope. The allocation will be on an equal ratio (1:1) between the two groups of interventions, stratifying by sex and by the stages I–III of Hoehn and Yahr scale (HY) [34]. To avoid bias, blinded testers will assess the participants.

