##### Secondary outcomes

The qualitative assessment about motivation, health empowerment, and the dependency of professional supervision at post follow-up period will be done by two researchers during an in-person interview, in a private room, and recorded for further transcription line-by-line and analysis. The questions will follow investigating the motivation in different steps of the study and are described in Table 3:

**Table 3 Tab3:** Distribution of questions in the study steps

Steps	Week	Question
Baseline	0	1. What made you seek physical therapy? 2. What does Parkinson’s disease mean in your life? 3. What are your expectations with physiotherapy?
Post-intervention	8	4. What this physiotherapy program meant in your life? 5. What did you think about the physiotherapy program that you participated? 6. After physical therapy, do you think you will be able to perform the exercises at home after discharge? What made you feel more or less capable? 7. Now at the end of the supervised treatment, what is your opinion of the expectations that you had at the outset?
Post follow-up	12	8. Were you able to do this exercise without supervision in your daily life? a) How was your experience? b) If you cannot do, what were the reasons? 9. After this period without supervision, what has this physiotherapy program meant in the last months of your life? 10. After your participation in this study, the reasons that make you seek physiotherapy are the same?

Note: Script assembled after pretest and familiarization with three individuals with PD.

The quantitative outcomes will investigate the preliminary effectiveness of the EMPOWER-PD on mobility, gait, fatigue, and aerobic function/endurance. Mobility will be assessed by the Timed up and Go test (TUG) which consists in walk a distance of 3 m, go beyond the horizontal mark located on the floor, turn on its axis, and return to sit again on the same chair. The time of all tasks will be timed and classified according to falls risk for PD individuals (< 11 s) [40, 41].

Gait will be evaluated by the Dynamic Gait Index (DGI) that assesses the gait in different sensorial contexts for eight tasks, which will be classified in a score of 0 to 3. The maximum score is the 24 points indicating a gait performance capable of adapting the different demands proposed by the test [42].

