### Procedures

The baseline assessment will be conducted once participants have given informed consent. All interviews/scales will be applied individually in a private setting by a blinded researcher, and all participants will receive an identification number. All evaluation will be performed in the afternoon, with individuals on the “on” phase of the medication. Demographics and eligibility criteria information will be collected at the baseline step. From there, the volunteers eligible in the inclusion criteria will be randomized into one of the two groups (EMPOWER-PD group and conventional physical therapy group) by a second researcher not involved in other steps.

Participants allocated to both groups will receive 8 weeks of intervention that will occur at the same time in different places to minimize individuals’ awareness of the differences between interventions. Then, the participants will be assessed at post-intervention, always by the same physiotherapist research, followed by a follow-up period of 4 weeks. The main objective of this stage of the study is to verify if the intervention would be a source of motivation/empowerment of health for a more proactive life, and in this way, decrease the dependency of professional supervision to remain active. For this, the participant will remain 4 weeks without any guidance from the therapist. After this, they will be contacted by phone to schedule the final evaluation, which will be performed on all outcome variables of the others stages of the study. Participants who drop out of the study will also be contacted by phone for the final evaluation.

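### Interview transcripts are labelled with the treatment arm by a researcher described as blinded, before a fourth researcher analyses them and categories are formed

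*Protocol article*

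**What the plan says.** The second aim in the Background is to "Compare the preliminary effectiveness of the EMPOWER-PD with the conventional physical therapy through qualitative analysis of motivation, empowerment of health", together with dependence on professional supervision after follow-up. For these outcomes "we hypothesize that the EMPOWER-PD will be associated with better outcomes in preliminary effectiveness than the conventional physical therapy".

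Under Secondary outcomes, "The qualitative assessment about motivation, health empowerment, and the dependency of professional supervision at post follow-up period" is made through recorded interviews at weeks 0, 8 and 12, with the questions listed in Table 3.

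Data management and analysis describes the handling of the recordings. Two authors transcribe, and two authors start coding. Then, once transcription is complete, "the corpus will be codified in numbers and their respective groups (e.g., # ID1emp, # ID5cph) by a blinded third researcher". The stated purpose of this step is "for the later analysis by a fourth researcher". Codes are next consolidated into categories by thematic analysis, and the whole team discusses the inferences.

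Elsewhere the article relies on blinding. Under Randomization, "To avoid bias, blinded testers will assess the participants". Under Procedures, "All interviews/scales will be applied individually in a private setting by a blinded researcher". The Abstract says that the participants are blinded to group.

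**The concern.** The label discloses the allocation. The Randomization section names the arms as "a) EMPOWER-PD or (b) conventional physical therapy (CPh"), so emp and cph are plain abbreviations of the arm names and not masked codes. The same sentence calls the person who writes these labels blinded, which cannot be true with respect to arm. The transcripts then go to the analyst with the arm in the identifier.

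Thematic analysis is interpretive. Deciding whether a remark expresses empowerment, and how remarks group into categories, leaves room for expectation. Here the expectation is declared in advance, and the team that developed EMPOWER-PD draws the inferences. What is at stake is the credibility of aim (ii): a reader told of blinded handling would credit the comparison with a protection that it does not have at its most subjective step.

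**Working it through.** The point turns on who sees the allocation and when, so the check is to set the steps in order. The only arithmetic is a count of interviews. The protocol gives no figure of its own to reproduce.

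**Order of steps in Data management and analysis**

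| Step | Who | Arm visible from the label? |
|---|---|---|
| Transcription | two authors | no |
| Start of coding | two authors | unclear |
| Labelling with number and group | third researcher, described as blinded | yes, by definition |
| Analysis | fourth researcher, blinding not stated | yes |
| Consolidation into categories | not stated | yes, follows the label |
| Inferences | whole team | yes |

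The second row is unclear because the sentence on first coding stands before the sentence on labelling, yet the labelling is itself timed only as coming after transcription. First coding could therefore be done on unlabelled or on labelled text. The rows from analysis onward are not ambiguous: the labels are applied for that later analysis, and nothing in the article says that the suffix is removed or replaced first.

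**Blinding statements elsewhere.** Blinding is stated for the participants, the researcher implementing randomization, the testers, the interviewer and the third researcher. It is not stated for the two first coders or the fourth researcher.

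**Number of interviews**

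- Participants: 12 per group × 2 groups = 24 (Sample size).
- Interview times: weeks 0, 8 and 12 (Table 3).
- Transcripts that could carry the label: 24 × 3 = 72.
- Baseline transcripts: 24 × 1 = 24. Their questions concern reasons for seeking therapy, the meaning of the disease and expectations, not the programme received.
- Transcripts from weeks 8 and 12: 24 × 2 = 48. These carry the comparison of arms.

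Both totals are maxima that assume full recruitment and no missed interviews.

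**What depends on these transcripts.** Motivation, empowerment and dependence on supervision are assessed by interview; the listed quantitative outcomes are mobility, gait, fatigue and endurance. The thresholds for going on to a later trial (recruitment and retention above 80%, adverse events below 5%) do not use the interviews.

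**The case against.** Several points on the other side are fair.

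- **No promise of analyst blinding is broken.** A reader might infer that the protocol commits to a blinded qualitative analysis and then breaches it. It does not: only the third researcher is called blinded, and the fourth researcher's status is not given. What stands is that the procedure as written hands over the arm, under a word that suggests otherwise.
- **Blinded may mean something else.** The article does not say blinded to what, and it also applies the term to the researcher who implements randomization. That supports asking for clarification. It does not rescue the sentence, because the person writing the suffix must know the arm.
- **Not all coding is shown to be exposed.** A reader might infer that every code is assigned with the arm in view. The position of the two authors' first coding is unclear, so this is not established.
- **The outcome is secondary, in a pilot.** The effectiveness claims are labelled preliminary and no feasibility threshold rests on them. This lowers the severity. Aim (ii) is nonetheless an explicit comparison of arms with a directional hypothesis, not purely exploratory qualitative work.
- **Other evidence exists.** Attendance and retention bear indirectly on motivation, and the Background links motivation to adherence. It would be too strong to say that nothing quantitative could support aim (ii), but neither measures empowerment or dependence on supervision.
- **Content will often reveal the arm.** Questions 4, 5 and 9 ask what the programme meant and what the participant thought of it, so masking can only be partial. That limits the benefit of neutral labels but is no reason to print the arm on every transcript.

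**Conclusion.** The point holds as a should-fix. The labelling sentence contradicts itself on blinding, and it gives the fourth researcher the allocation before the interpretive analysis and before the categories are formed. Up to 48 interviews are mainly affected. Counting all 72 as equally exposed would overstate it, since the 24 baseline interviews do not ask about the programme.

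The size of any bias cannot be derived from the document. A reader might infer that the result will be tilted towards EMPOWER-PD. The stated hypothesis and the developers' part in the analysis make that the plausible direction, but they do not demonstrate it. Nor does the problem reach the primary outcomes or the criteria for a future trial.

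The conclusion assumes that the suffixes reach the fourth researcher in the form shown in the examples, as the text reads. If they are in fact stripped beforehand, the article needs only to say so.

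**What to change.** 1. Label transcripts with neutral identifiers only (for example ID1 to ID24), and have someone outside the analysis hold the arm key.
2. Complete the coding and fix the categories on the pooled corpus, and only then attach the arm to compare themes.
3. State where the two authors' first coding falls relative to labelling, and who is blinded to what.
4. Keep programme-specific content in the transcripts. Primary outcomes assigns acceptability to this analysis, and deleting such content would weaken it. State instead that content may reveal the arm and that masking is partial.

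The cost is small: handling the key and a later comparison of arms. The team's final inferences will still be drawn with the arm known, but on categories already fixed.

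Trial status gives October 2018 as the end date, so this may come too late. If coding has already been done with arm labels, remove the word blinded from the labelling step and report the qualitative comparison as unblinded.

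### Aim (ii) expects EMPOWER-PD to be better on motivation, empowerment and independence, but the planned route to that conclusion has no tally by arm, no criterion for better, and readable arm labels

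*Protocol article*

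**What the plan says.** **The aim and its direction.** In the protocol article, Background, aim (ii) is to "Compare the preliminary effectiveness of the EMPOWER-PD with the conventional physical therapy through qualitative analysis of motivation, empowerment of health". It adds dependence on professional supervision after the follow-up period. For these outcomes the same section states: "we hypothesize that the EMPOWER-PD will be associated with better outcomes in preliminary effectiveness than the conventional physical therapy". For motor and non-motor symptoms it expects only similar results.

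**The data.** Under Secondary outcomes, the constructs are explored in individual interviews, "recorded for further transcription line-by-line and analysis". Table 3 lists ten mostly open questions at weeks 0, 8 and 12. No scale or score is used. Question 8, at week 12, asks: "Were you able to do this exercise without supervision in your daily life".

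**The analysis.** Data management and analysis gives this sequence:

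- Two authors transcribe, and two authors start the coding.
- A blinded third researcher labels the material: "the corpus will be codified in numbers and their respective groups". The examples given are an ID number followed by *emp* or *cph*.
- A fourth researcher analyses it.
- Categories are then built: "Codes will then be consolidated into categories after an extensive exploration of the material". The method named is a thematic one.
- The conclusion is reached in a last step: "From this, entire research team will discuss to formulate inferences".

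**Intervals.** The same section promises 95% confidence intervals for all preliminary efficacy results. That sentence stands in the paragraph on quantitative outcomes, but the Abstract also places the qualitative assessment under preliminary efficacy.

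**The concern.** A hypothesis that one randomised arm does better needs something measured on each participant, compared between arms, with a stated idea of what result would count for or against it. The article describes the path from recording to inference, and none of these three elements appears on it.

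Two features add to the problem. The arm can be read from the corpus label, so the analyst who forms the categories is not masked by the labelling step. The final step is a discussion by the whole team, whose hypothesis favours one arm and who say in the Discussion what they believe the approach will provide.

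Among the secondary outcomes, these are the only ones on which EMPOWER-PD is expected to be superior. If superiority is reported from themes and discussion, readers of the pilot, and planners of the definitive trial, cannot tell how many participants in each arm lie behind it or how far chance could explain it.

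**Working it through.** **1. Inputs**

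| Item | Value | Source |
|---|---|---|
| Participants per arm | 12 (upper end of 6–12) | Sample size |
| Target total | 24 | Abstract |
| Allocation | 1:1 | Randomization |
| Alpha, power, effect size or margin for aim (ii) | none stated | – |

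**2. The plan's own figure.** 2 × 12 = 24, which reproduces the target. There is no other figure for aim (ii) to recompute.

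**3. What the comparison needs, set against what is stated**

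| Needed | Stated |
|---|---|
| Individual data in both arms | Yes: individual interviews, the same questions in both arms |
| Link from extract to person and arm | Yes: ID and arm label |
| Classification of each participant on each construct | No |
| Count by arm and between-arm difference | No |
| Criterion for better, same or worse | No |
| Analyst masked to arm | No: the label shows the arm |
| Uncertainty | 95% interval promised for preliminary efficacy, but no quantity defined here to which it could apply |

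The first two rows show that the gap can be closed from data already planned. The other rows are the gap.

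**4. How uncertain a tally by arm would be (illustration).** The documents give no rates, so the counts below are assumed. For x of n, with p = x/n and z = 1.96, the Wilson limits are

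[p + z²/(2n) ± z·√(p(1−p)/n + z²/(4n²))] / (1 + z²/n).

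With limits (l₁, u₁) and (l₂, u₂) for the two arms, the Newcombe limits for d = p₁ − p₂ are

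- lower: d − √[(p₁ − l₁)² + (u₂ − p₂)²]
- upper: d + √[(u₁ − p₁)² + (p₂ − l₂)²].

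*6 of 12 against 6 of 12.* The Wilson half-width is 1.96 × √(0.02083 + 0.00667) / 1.3201 = 0.246, giving limits 0.254 and 0.746. The difference is 0 ± √(0.246² + 0.246²) = ±0.348.

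*9 of 12 against 6 of 12.* The Wilson limits for 9 of 12 are 0.468 and 0.911.

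- Lower: 0.25 − √(0.282² + 0.246²) = −0.125.
- Upper: 0.25 + √(0.161² + 0.246²) = 0.544.

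| EMPOWER-PD | CPh | Difference (points) | 95% interval (points) |
|---|---|---|---|
| 6/12 | 6/12 | 0 | −34.8 to +34.8 |
| 9/12 | 6/12 | +25 | −12.5 to +54.4 |
| 6/12 | 3/12 | +25 | −12.5 to +54.4 |
| 10/12 | 4/12 | +50 | +10.6 to +72.9 |

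The third row shows what is at stake. A theme voiced by twice as many people in one arm as in the other is compatible with no difference, and nothing in the stated analysis would show this. An exact interval, as proposed in the fix, is somewhat wider than these.

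**The case against.** **The case on the other side.** Thematic analysis is a recognised method and suits a pilot. Sample size was set by qualitative practice and saturation, and no test is planned. Coding, labelling and analysis precede the discussion, and nothing says the discussion may override the categories. The progression thresholds under Primary outcomes do not use these results, and the Discussion leaves effectiveness to a definitive trial. A condensed article may also leave a coding frame to a fuller document.

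**What stands.** The method is legitimate, no progression decision depends on aim (ii), and the absence of a detailed coding frame is not a fault here. The fault is a mismatch within the article: it fixes a better-than hypothesis and states a route to the conclusion that contains no comparison.

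**Stronger readings that a reader might infer, and that the documents do not support:**

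- *The data could not refute the hypothesis.* They could. Both arms get the same questions, several invite unfavourable answers, and reports of failure in EMPOWER-PD or equal success in CPh would count against it. What is missing is a stated rule.
- *There is no per-participant information, or the numbers behind a theme are lost.* Interviews are individual and labelled by ID, and question 8 can be answered yes or no. The counts are recoverable but not planned.
- *The plan would treat differences short of statistical significance as findings.* It sets no threshold in either direction. A Fisher-type cut-off is not a standard that this unpowered pilot adopts.
- *Those who deliver the sessions decide the result.* The article says the entire research team. It does not say whether the treating therapists belong to it.

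**Conclusion.** The concern holds in this limited form: a directional comparison of randomised arms is paired with an analysis that has readable arm labels, categories formed after exploration, inference by team discussion, no tally by arm and no criterion. Followed as written, it is open to expectation and cannot state the uncertainty of the comparative claim.

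The size of any resulting bias cannot be calculated from the documents. What can be shown is the imprecision left unreported: about ±35 points at equal rates of 50% with 12 per arm. This assumes full recruitment, a yes/no classification and no missing interviews. The rates are illustrative.

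The point concerns a secondary aim and does not touch the primary feasibility outcomes. It is still worth correcting, because the remedy uses data already planned and these are the only secondary outcomes on which an advantage is hypothesised.

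**What to change.** 1. Keep the thematic analysis unchanged in method, and present it as description.
2. Replace the arm suffix with a neutral ID until codes and classifications are final. Interview content may still reveal the arm, so this reduces the problem without removing it.
3. Before unmasking and before the team discussion, have the analyst already in the plan classify each participant on items fixed in advance. The minimum is question 8, coded as able or not able to exercise unsupervised. It bears on independence only. If motivation and empowerment are to be compared between arms, each needs its own pre-set item.
4. Report the count and the number interviewed in each arm, with the difference and an exact 95% confidence interval, as a descriptive estimate and not a test.
5. Word aim (ii) as exploratory, and do not conclude that EMPOWER-PD is better from themes or discussion alone.

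**Cost.** About 24 transcript sets to classify, with no new data collection. Some detail is reduced to counts, although the full thematic report remains. The intervals will be wide and will seldom support a firm comparative statement, which is a fair reflection of what 12 per arm can show.

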**Method:**

A 12-week pilot for a randomized clinical trial will assess the feasibility and preliminary effectiveness of the EMPOWER-PD and make comparisons with conventional physical therapy (CPh). Both protocols consist of mobility and locomotion training, and aim at improving motor and non-motor symptoms through different approaches. The EMPOWER-PD aims to provide a source of motivation and empowerment of health through the self-knowledge of the individual’s abilities and limitations, in a protocol that addresses individual preferences. The CPh is based only on physiotherapist decisions, not addressing the individual’s preferences or motivation/empowerment. The target recruitment will be 24 PD individuals, between stages I and III of Hoehn and Yahr (HY), who will be recruited from Brazilian Parkinson’s disease Rehabilitation Initiative (BPaRkI) with allocation ratio 1:1. A computerized block randomization procedure will be implemented by a blinded researcher with the participants blinded to group assignment. The sessions will be conducted in a group setting, twice a week, during 60 min for 8 weeks, followed by 4 weeks of follow-up. The primary outcomes will be the feasibility data (adherence, recruitment rate, and safety). The secondary outcomes will assess the preliminary efficacy on qualitative assessment about individual’s motivation/empowerment and quantitative motor outcomes (Timed Up and Go and Dynamic Gait Index) and non-motor symptoms (6-min walk test and Fatigue Severity Scale). The recommendation to have 6–12 participants per group will be adopted based on the qualitative analysis to the sample size.

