#### Sample size

The primary outcome of this pilot for a randomized clinical trial will be the feasibility (adherence, recruitment rates and safety). As in feasibility studies a formal sample size calculation is not required [30], we estimated the number of participants based on qualitative analysis. We will adopt the recruitment of 6–12 participants per group as a recommended for qualitative studies, being adopted the major value (*n* = 12 per group) [31]. Accordingly, we will use the criteria of sampling saturation that means “collecting data until no new information is obtained” [32].

In relation to the quantitative variables, the present study is not intended to be fully powered for detection of statistically significant effects, but it will enable a sample size calculation related to the quantitative variables for a future randomized trial [33]. For that, we plan to select the sample size based on reasonable precision of estimates of standard deviation of quantitative measures which have shown sensitivity in this feasibility study.

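### Allocation is stratified by sex and Hoehn-Yahr stage, but the stated analysis of the quantitative outcomes has no stratum term; if stage or sex is prognostic, a plain between-arm 95% CI is wider than the design warrants

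*Protocol article*

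**What the plan says.** *Randomization*: "A computerized block randomization procedure will be implemented by a blind researcher", with a 1:1 ratio, "stratifying by sex and by the stages I–III of Hoehn and Yahr scale (HY"). No block size or grouping of stages is given.

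*Data management and analysis*, on the quantitative outcomes: "the descriptive analysis will be performed with frequency, central tendency, and variability (mean and standard deviation or median and interquartile interval"). The next sentence reads "All results of the preliminary efficacy of the feasibility trial will be described as estimates of 95% confidence interval". No model, covariate or stratum is named. The text does not say whether the intervals are per arm or for the difference, but aim (iii) in *Background* compares the two arms on motor and non-motor symptoms by means of 95% confidence intervals, so a between-arm interval is intended.

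*Sample size*: 12 per group, from a recommendation for qualitative studies. The pilot is not meant to be powered for effects. Its SDs are to support the next trial: "we plan to select the sample size based on reasonable precision of estimates of standard deviation of quantitative measures".

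**The concern.** Blocking within strata makes the arms alike on sex and stage. Where those factors predict the outcome, the difference between arms varies less over repeated randomisations than two independent samples would suggest. An interval built from the raw arm SDs puts the stratum-related spread back into the standard error. It then covers more than 95% of the time, and the precision that stratification could give goes unused.

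Two uses of the results are affected. First, the 95% CI is the only tool named for the between-arm comparison in aim (iii). For these outcomes the article hypothesises similar effectiveness, and a wider interval makes similarity harder to support. Second, the SD is an output meant for sizing the next trial. The raw and the stratum-adjusted SD answer different design questions, and the article does not say which will be carried forward.

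**Working it through.** **Inputs from the article.** 12 per group; 2 × 12 = 24, which agrees with the target in the abstract. 95% confidence. Sex (2 levels) and stages I, II and III. If each stage is its own level, there are 2 × 3 = 6 strata, averaging 24/6 = 4 people each.

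**Assumed, because the article gives none.** R2, the share of outcome variance explained by the strata; the stage mix; the block size.

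**Step 1: half-width with 12 v 12, in units of the raw SD.**
- Plain: t(0.975, 22) × √(2/12) = 2.074 × 0.408 = 0.85.
- Adjusted for sex and one ordered stage term (two degrees of freedom fewer): t(0.975, 20) × √(1 − R2) × √(2/12) = 2.086 × 0.408 × √(1 − R2) = 0.85 × √(1 − R2).
- Adjusted, by R2: 0.85 at 0; 0.79 at 0.15; 0.71 at 0.30; 0.63 at 0.45.

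**Step 2: simulation, which allows for incomplete blocks.** 24 people, blocks of 2 or 4 within six strata, stage mix 25/50/25%, 40% in one sex, a linear stage effect and no sex effect, 8,000 trials per setting. Mean half-widths in SD units:

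| Assumed R2 | Plain | Adjusted (arm + sex + ordered stage) | Plain relative to adjusted |
|---|---|---|---|
| 0 | 0.84 | 0.85-0.86 | 1-2% narrower |
| 0.15 | 0.84 | 0.78-0.79 | about 7% wider |
| 0.30 | 0.84-0.85 | 0.71-0.72 | about 18% wider |

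For example, with blocks of 4: 0.842/0.789 = 1.07 and 0.843/0.715 = 1.18. The plain 95% interval misses the true difference 3.5-3.8% of the time at R2 0.15 and 2.2-2.8% at 0.30, instead of 5%.

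**Step 3: other ways to adjust.** A second simulation (blocks of 4, stage mix 20/50/30%) gave these adjusted/plain ratios:
- Stage as three categories plus sex: 1.03 at R2 0, 1.00 at 0.05, 0.92 at 0.20, 0.86 at 0.30.
- All six cells: 1.05 at R2 0, 1.00 at 0.10, 0.94 at 0.20, 0.88 at 0.30.

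Break-even is therefore near R2 0.05 for three categories and 0.10 for six cells; the single ordered term breaks even below 0.05. With four people per cell, the small model is the sensible one.

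**Step 4: the SD for the next trial.** In the second simulation the raw pooled SD averaged 0.99-1.00 of the true overall SD at every R2, so it is not biased upwards. The residual SD averaged 0.94, 0.88 and 0.83 at R2 0.10, 0.20 and 0.30.

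Illustration with an assumed difference of 0.5 SD, 80% power and two-sided 5%:
- n per arm = 2 × (1.96 + 0.84)² × (1 − R2)/0.5².
- Raw SD (R2 = 0 in the formula): 63 per arm.
- Residual SD: 57, 51 or 44 per arm at R2 0.10, 0.20 or 0.30.
- If a trial of that smaller size were then analysed without adjustment, its power would be 76%, 71% or 65%.

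Either SD is imprecise here: on 22 degrees of freedom its 95% limits are 0.77 to 1.42 times the estimate.

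**The case against.** The strongest reply is that the article is silent rather than wrong. It never calls the intervals unadjusted, and a fuller plan may name a model. A reader might infer that the sponsor has decided to disregard the strata; the text does not support that. It does name its method, however, and that method is a plain descriptive one, so asking for one clarifying sentence is fair.

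The reply also has force on size. The article reports no link between stage or sex and any of the four outcomes. It calls gait a potent indicator of disability, but the step from there to Hoehn-Yahr stage is the reviewer's. The simulations gave explanatory power to stage only, so they show nothing about sex. Outcomes are also measured at baseline, and if the intervals are for change, part of the stage-related spread may already cancel. All of this stands, and it makes the point conditional.

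Finally, these are secondary outcomes in a pilot that plans no hypothesis test, so loss of power is not a consequence for this trial. The error is conservative for claiming a difference, though less comfortable for the hypothesis of similarity.

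**Conclusion.** The point holds in conditional form. The allocation uses sex and stage and the stated analysis does not. If those factors predict an outcome, a plain between-arm interval is wider than the design warrants: about 7% at R2 0.15 and 18% at R2 0.30. If they do not, adjusting costs 1-2%. R2, the stage mix, the block size and a linear stage effect are assumptions.

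Two stronger readings are tempting and not supported. One is that the intervals are certainly too wide; at R2 near 0 they are not. The other is that the SD kept for the next trial is too large. The raw SD is the right input for an unadjusted trial, and exceeds what is needed only if that trial commits to the same adjustment. The article fixes neither the future analysis nor which SD will be used.

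Severity is low. No stated figure changes and the sample size stays at 24.

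**What to change.** In *Data management and analysis*, state that for Timed Up and Go, Dynamic Gait Index, 6-min walk and Fatigue Severity Scale the between-arm difference and its 95% CI come from a linear model with arm, sex and Hoehn-Yahr stage as one ordered term. The descriptive summaries by arm can stay, including medians where the data call for them.

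In *Sample size*, state that both the raw and the residual SD will be reported, and that the next trial will be sized on the one that matches its planned analysis: the residual SD only if that trial commits to the same adjustment, the raw SD otherwise.

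The cost is wording. Both factors are already recorded for randomisation and the model runs in the named software. The price is two degrees of freedom, which widens the interval by 1-2% if the strata prove unrelated to the outcome. One ordered term also assumes a roughly even trend across stages.
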